#### Exploratory Analysis

Patterns among individuals with respect to going back and changing responses to previous questions will be investigated in exploratory analyses using a combination of regression and clustering models. We will also run sensitivity analyses to see if the primary findings change when using the first response option that participants chose.

### Sample Size

The trial will use a Bayesian group sequential design [35-37] to monitor recruitment, with interim analyses planned for every 50 participants completing the questionnaire. Responses to each of the 10 COS outcomes will be modelled following the primary analyses, and each dummy variable representing cluster order will be assessed for evidence of effect or futility. Let ß_k,i_ represent the coefficients for each dummy variable (i=1,2,3) in each model (k=1...10) and D represent the data available at the interim analyses. Then, the target criteria will be (1) *effect:* p(ß_k,i_ > 0 | D) > 97.5% or p(ß_k,i_ < 0 | D) > 97.5% (ie, if the question order effect is greater or less than 0 with a probability greater than 97.5%); (2) *futility (normal regression):* p(−0.1 < ß_k,i_ < 0.1 | D) > 95% (ie, if the question order effect is close to 0 with a probability greater than 95%); and (3) *futility (negative binomial and logistic regression):* p(log(1/1.2) < ß_k,i_ < log(1.2)) > 95% (ie, if the question order effect is close to 0 with a probability greater than 95%).

For the effect criterion, we will use a skeptical normal prior for dummy covariates (mean 0, SD 1.0), and a wider prior will be used for the futility criterion (mean 0, SD 2.0).

The criteria should be viewed as targets; thus, at each interim analysis, we will evaluate each criterion for each covariate and decide if we believe that recruitment should end. We will only make decisions to stop recruitment entirely, not drop or modify any of the arms. Simulations indicate that we will require a sample size in the range of 1500 to 2500 participants. Recruitment will not exceed 24 months.

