#### Primary Analysis

The primary analysis of question order bias will be conducted through regression models in which each outcome in each cluster will be regressed against a dummy variable representing whether each of the other clusters was asked before or after the outcome. For instance, standard drinks consumed in the past week (which is part of Cluster 2), will be regressed against 3 dummy variables, representing Cluster 1, Cluster 3, and Cluster 4, respectively. The dummy variables will take value 0 if the cluster was asked after Cluster 2 and value 1 if the cluster was asked before Cluster 2. For each outcome, 1 regression model will be created, yielding a total of 10 models, using negative binomial regression for counts (outcome 6 and outcome 9), logistic regression for hazardous or harmful drinking (outcome 5, using AUDIT-C scores of 5+ as the cutoff), and normal regression for scores (all other outcomes, possibly log-transformed if found to be skewed).

We will investigate 2- and 3-way interactions among the cluster dummy variables in order to explore if the order of a combination of clusters affects outcomes (eg, if the order of Cluster 1 and Cluster 2 in combination creates a question order bias on the outcomes in Cluster 3).

The proportion of participants abandoning the questionnaire will be analyzed in two ways: (1) using a logistic regression model with allocated arm as a covariate, to identify orders that are more (or less) likely to result in abandonment, and (2) using a logistic regression model with the cluster that was abandoned and the number of questions responded to as covariates, to identify clusters that are more (or less) likely abandoned (adjusted for number of questions responded to).

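### The whole trial can be stopped by judgement over 30 coefficients viewed every 50 completers, with no minimum size and no stated combination of targets, while with no order effects some coefficient nearly always meets the effect target.

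*Protocol article*

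**What the plan says.** The Primary Analysis section regresses each outcome on three before/after dummies, one for each of the other clusters: "For each outcome, 1 regression model will be created, yielding a total of 10 models".

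The Sample Size section uses these models for a Bayesian group sequential design, "with interim analyses planned for every 50 participants completing the questionnaire". At each look, "each dummy variable representing cluster order will be assessed for evidence of effect or futility". The effect target is met "if the question order effect is greater or less than 0 with a probability greater than 97.5" percent. Futility needs more than 95% posterior probability within ±0.1 (normal models) or ±log(1.2) (logistic and negative binomial models). For the effect target, "we will use a skeptical normal prior for dummy covariates (mean 0, SD 1.0"; the futility prior has SD 2.0.

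On acting on the targets: "The criteria should be viewed as targets; thus, at each interim analysis, we will evaluate each criterion for each covariate and decide" whether recruitment should end. The stop is for the trial as a whole: "We will only make decisions to stop recruitment entirely, not drop or modify any of the arms". On size: "Simulations indicate that we will require a sample size in the range of 1500 to 2500 participants". The only hard limit is 24 months.

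Separately, the Preliminary part of the Analysis section complements posterior inference with null hypothesis tests at the .05 level.

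**The concern.** Thirty coefficients each have their own targets, but there is one stopping decision, and the article links the two only by what the team believes after seeing the results. It does not say whether one, some, most or all coefficients must be resolved, or from what sample size a stop is allowed. The 97.5% threshold is the same at every look and for every coefficient.

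Two things are at stake. First, a coefficient that has crossed by chance can be used to support stopping. An estimate that crosses early must be large to do so, so it would be exaggerated, and the other coefficients would be left with little data. Second, tests at .05 do not hold 5% when the time of stopping may depend on the accumulating results. The findings are meant to guide how future trials ask the core outcome set, so a spurious order effect would be passed on to them.

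**Working it through.** **Inputs from the article.** 10 models × 3 dummies = 30 coefficients. A look every 50 completers gives 1500/50 = 30 to 2500/50 = 50 looks. (The range is in participants and the looks in completers; completers are used here.) Allocation is equal over 24 orders.

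**Inputs assumed.** Unit-SD Gaussian outcomes and no order effects. Outcome correlations within/between clusters were varied over 0/0, 0.5/0.3, 0.8/0.5, 0.9/0.7 and an extreme 0.98/0.9. One variant used raw-scale SDs up to 8.

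**Precision of one coefficient.** Each dummy has variance 1/4, and the three dummies in a model correlate 1/3. The variance inflation is (1 + 1/3) / [(1 − 1/3)(1 + 2/3)] = 1.2. Hence variance = 1.2 × 4σ²/n = 4.8σ²/n.

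**The plan's own figure.** The 1500 to 2500 range cannot be reproduced as a simulation result, because the assumed effects, SDs, correlations and stopping combination are not given. It is of the right order for a single coefficient with σ = 1:
- Futility with an estimate of exactly 0: n = 4.8 × [(1.96/0.1)² − 1/2²] = about 1843. With the estimate 0.5 or 0.67 standard errors from 0, n is 2283 or 2609.
- A 0.15 SD effect meets the effect target with 80% probability at 4.8 × (1.96 + 0.84)²/0.15² = about 1674, and with 90% at about 2242.

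**Effect target with no order effects.** A posterior probability above 97.5% is about |posterior mean/SD| > 1.96. For one look and independent coefficients, 1 − 0.95^30 = 79%. Over all looks up to N = 1500 to 2500, by simulation:

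| Correlation within/between | At least one coefficient meets the effect target at some look |
|---|---|
| 0/0 and 0.5/0.3 | 100% |
| 0.8/0.5 | 99.4% to 100% |
| 0.9/0.7 | 98.2% to 99.6% |
| 0.98/0.9 | 94.9% to 96.6% |
| 0.8/0.5, raw-scale SDs | 98.6% to 99.8% |

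- The median first crossing is at 50 to 100 completers.
- A given coefficient crosses at some look in about 27% to 32% of trials, or 23% to 27% with raw-scale SDs.
- Counting only looks from 500 to 1500, the any-of-30 figure is still 91% to 99.6%.

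**Size of a spurious estimate.** To cross at n = 50, an estimate must be about 1.96 × √(4.8/50) = 0.61 SD. At n = 1500 it must be about 1.96 × √(4.8/1500) = 0.11 SD.

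**Protection from the prior.** Shrinkage under N(0, 1) is about SE²/(1 + SE²). At n = 50 this is 0.096/1.096 = about 9%. At n = 2000 it is 0.0024/1.0024 = about 0.2%. It grows with the outcome's SD, and the article does not say that scores are standardised.

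**If all 30 had to be resolved.** With no order effects, on average about 5 of 30 coefficients meet futility at N = 1500 and 16 to 17 at N = 2500. All 30 meet effect or futility in at most 0.2% of trials. This takes SD 1 for the normal outcomes, a log-scale SD of 1 for counts and an event proportion of 0.5 for the binary outcome.

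**The case against.** A reader might infer that one crossing ends the trial, so that a null trial would nearly always stop early on a false signal. The article does not say so. It calls the criteria targets and reviews all of them, and a team expecting 1500 to 2500 participants can hardly intend a rule usually met at 50 to 100. At any one late look only about 1.2 to 1.7 of the 30 coefficients are flagged by chance, so the team would see mostly unflagged results. This stands: the percentages above are not stopping probabilities, and those cannot be computed without a rule.

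A reader might also infer that 1500 to 2500 is wrong. That is not supported. The simulation assumptions may be in the full protocol, and the range is plausible for one coefficient. The supportable statement is that it cannot be reproduced from the article. Nor does the prior give no protection: it is weak and depends on scale.

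Finally, non-binding Bayesian targets are a deliberate and disclosed choice, and the posterior does not formally depend on the stopping rule. This stands for the posterior given its prior. It does not cover the .05 tests, whose error rate depends on the looks, and a prior that shrinks so little does not much temper early crossings. An unseen analysis plan could add a rule, but the article does more than leave one out: it states that the decision is by judgement.

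**Conclusion.** The point holds as a weakness in how the stop is fixed. It does not show that the trial will stop wrongly. The article allows a trial-wide stop by judgement over 30 coefficients every 50 completers, with no floor and no combination of targets. With no order effects, a met effect target is available at some look in about 95% to 100% of trials, first typically at 50 to 100 completers with a spurious estimate of about 0.6 SD. A given coefficient meets it in about 23% to 32%. The complementary .05 tests therefore cannot be taken to hold 5% under such stopping.

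The figures rest on a Gaussian approximation for all ten models and on assumed correlations. Early-look rates for the logistic and negative binomial models may differ. The any-of-30 conclusion hardly moved over the correlations tried. The change is worth making, though the flaw does not invalidate the design.

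**What to change.** 1. Allow no stop before 1500 completers, the plan's own lower bound, with the 24-month limit unchanged. Over looks from 1500 to 2500 this lowers the per-coefficient false-signal rate from about 30% to about 12%, and the typical spurious estimate from about 0.6 to 0.12 SD.
2. State in advance which coefficients, or what share of them, must have met effect or futility before stopping. Do not require all 30: that is practically never met by 2500 and would simply run to 24 months.
3. Rerun the simulations under that exact rule, and restate the expected sample size with its false-signal rate and assumptions.
4. The floor does not remove the any-of-30 signal, which stays at about 90% to 97% for low to moderate outcome correlations and is lower when they are very strong. Report that rate or use a stricter effect threshold. For scale, holding it to 5% over 30 to 50 looks needs |z| of about 3.6 to 3.9, a posterior probability of about 99.98% to 99.99%.
5. Do not present the .05 tests as holding 5% under repeated looks.

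The cost is a few sentences and a rerun of existing simulations. The team loses some discretion, and the restated size may be less favourable. A stricter threshold would also make real order effects slower to declare.

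### The stated 1500 to 2500 participants does not deliver the futility target across that range: for outcome 5 it is out of reach below about 2219, and for the scores it depends on an unstated SD

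*Protocol article*

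**What the plan says.** The Sample Size section of the protocol article plans interim analyses after every 50 completers. At each one, the three order coefficients in each of ten models are judged for effect or futility.

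- Effect: "if the question order effect is greater or less than 0 with a probability greater than 97.5" per cent.
- Futility, normal regression: "p(−0.1 < ß_k,i_ < 0.1 | D) > 95" per cent.
- Futility, logistic and negative binomial regression: "p(log(1/1.2) < ß_k,i_ < log(1.2)) > 95" per cent.
- Prior for futility: "a wider prior will be used for the futility criterion (mean 0, SD 2.0").

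The futility criterion is glossed as "if the question order effect is close to 0 with a probability greater than 95" per cent. The section calls the criteria targets, limits recruitment to 24 months and concludes: "Simulations indicate that we will require a sample size in the range of 1500 to 2500 participants".

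Under Primary Analysis, each outcome is regressed on three dummies that record whether each other cluster came before or after it. Outcome 5 uses "logistic regression for hazardous or harmful drinking (outcome 5, using AUDIT-C scores of 5+ as the cutoff"). Most other outcomes use normal regression on scores, which may be log-transformed. Standardisation is not mentioned, and no SD or prevalence is given.

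**The concern.** A coefficient whose true value is zero can properly be settled only by the futility criterion. Whether 1500 to 2500 is enough therefore depends on whether a posterior at that size can be narrow enough to put 95% of its mass inside the margin. If it cannot, a coefficient may meet neither target even when the estimate is exactly zero.

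The Discussion hopes the findings will raise confidence in using the core outcome set. That needs a supported statement that order does not matter. The risk is that an unresolved coefficient is read as absence of order bias.

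**Working it through.** **The plan's own figure.** The range of 1500 to 2500 cannot be reproduced, because the simulation inputs are not given. What can be checked is whether any inputs could make the futility target attainable at those sizes.

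**Variance of a coefficient.** Inputs: equal allocation to the 24 orders (Table 1; Randomization and Blinding) and three before/after dummies per model (Primary Analysis).

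- Each dummy has mean 1/2 and variance 1/4.
- Two given clusters both precede a third in 1/3 of the orders, so the covariance is 1/3 − 1/4 = 1/12 and the correlation is (1/12)/(1/4) = 1/3.
- Regressing one dummy on the other two gives R² = 2(1/3)²/(1 + 1/3) = 1/6, so the variance inflation is 1/(1 − 1/6) = 1.2.
- Normal regression: Var(β) = 1.2 × 4 × SD²/N = 4.8·SD²/N.
- Logistic regression: Var(β) = 4.8/(N·p(1 − p)), which is smallest at p = 0.5, where it is 19.2/N.

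The N(0, SD 2) prior adds a precision of only 0.25, worth about 0.25 × 19.2 ≈ 5 participants in the logistic case and about 1 for a unit-SD score.

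**Best case.** With an estimate of exactly zero, the posterior probability inside a margin m is 2Φ(m/SE) − 1. Reaching 95% needs SE ≤ m/1.96.

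- Score: N ≥ 4.8·SD²·(1.96/0.1)² ≈ 1844·SD².
- Outcome 5, with log 1.2 = 0.1823: N ≥ [4.8/(p(1 − p))]·(1.96/0.1823)², which is 2219 at p = 0.5.

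**Outcome 5.**

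| Prevalence of AUDIT-C 5+ (assumed) | Minimum N | Best probability at 1500 | Best probability at 2500 |
|---|---|---|---|
| 0.5 | 2219 | 89.3% | 96.3% |
| 0.7 | 2641 | 86.1% | 94.4% |
| 0.8 | 3467 | 80.4% | 90.4% |

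The first row needs no assumption about the population, because p = 0.5 is the most favourable value. The target is therefore out of reach over (2219 − 1500)/1000 ≈ 72% of the stated range. At 2500 it requires p(1 − p) ≥ 0.2219, that is, a prevalence between about 33% and 67%.

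**Chance of meeting it at 2500, outcome 5, true effect zero, p = 0.5.** SE = √(19.2/2500) = 0.0876. The estimate must fall within ±0.032, which has probability 28%. In 20,000 simulated trials with looks every 50, the chance at any look up to 2500 was 36%.

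**Scores.** The largest residual SD for which ±0.1 is attainable is √(N/1844): 0.90 at N = 1500 and 1.16 at N = 2500. With SD 1 (an assumption):

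- At 1500, SE = √(4.8/1500) = 0.0566 and the best probability is 92.3%.
- The minimum N is 1844.
- At 2500, SE = 0.0438 and the estimate must fall within ±0.027, which has probability 46% (58% at any look).

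Across assumed SDs, the minimum N is 461 at SD 0.5, 1180 at SD 0.8 and 7376 at SD 2.

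**Negative binomial outcomes (assumed inputs only).** Minimum N = 4.8·(1/mean + dispersion)·(1.96/0.1823)².

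- Outcome 6, mean 20 and dispersion 1: about 582.
- Outcome 9, mean 0.3 and dispersion 2 to 5: about 2958 to 4623.

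**The case against.** The strongest reply is that the protocol never says 1500 participants will satisfy futility for every coefficient. The range belongs to a sequential design in which either an effect or futility settles a coefficient. For the effect criterion it is ordinary: at SD 1 and an 80% chance at a single look, it corresponds to effects of 2.80 × 0.0566 ≈ 0.16 at 1500 and 2.80 × 0.0438 ≈ 0.12 at 2500. The criteria are targets, and the only hard limit is 24 months. The most favourable minimum for outcome 5 (2219) and the unit-SD minimum (1844) lie inside the range. Simulation details may also sit in a fuller document.

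Much of this stands. It rules out calling the range a breach of a rule, and the missing simulation inputs are not themselves the point. It does not remove the bound for outcome 5: no simulation input can lift that probability above 89.3% at 1500.

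A reader might go further in three ways that the documents do not support.

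- *Most truly null coefficients would end unresolved.* This fails for unit-SD scores. At 2500, about 46% meet futility and another 5% meet the effect criterion by chance, roughly 51% together, and 58% meet futility at some look.
- *Futility is impossible throughout the range, or for all outcomes.* It is attainable in the upper part under favourable inputs, at 1500 for scores with SD below about 0.90, and probably early for outcome 6.
- *The planners overlooked the correlation between dummies.* Ignoring it gives a unit-SD minimum of 1537, near 1500, but that still exceeds 1500 and is no evidence of how the range was obtained.

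**Conclusion.** The point holds as a mismatch between the stated size and the stated futility margins. For outcome 5 it rests only on the 24-order design, the log 1.2 margin and the 95% threshold: futility is unattainable below about 2219. At 2500 it has at most about a 28% chance per coefficient under a true zero (36% at any look), and none if prevalence is outside about 33% to 67%. Prevalence is not documented, but recruiting people who search for help with drinking makes a value above 67% plausible.

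For scores the conclusion is conditional on the residual SD: attainable at 1500 below about 0.90, at 2500 below about 1.16, and nowhere in the range above that. Figures for outcomes 6 and 9 rest wholly on assumed means and dispersions and carry no weight in the conclusion.

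**What to change.** Rerun the simulation with the actual design (variance 4.8·SD²/N for scores, with outcome-specific SD and, for outcome 5, a range of AUDIT-C 5+ prevalence). Restate the sample-size sentence so that 1500 to 2500 is not presented as enough to meet futility for outcome 5, or for scores with a larger SD. If the range was driven mainly by the effect criterion, say so.

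Add one sentence, fixed before the data are seen: a coefficient that meets neither target is reported as inconclusive, not as showing no order effect.

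The cost is one simulation rerun, a reworded paragraph and a less favourable stated figure. No increase in enrolment is needed.

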## Results

Recruitment will commence in November 2020. Findings from this study are expected to be disseminated in peer-reviewed journals and presented at relevant international conferences during 2021-2023, after which all data will be made available on the Open Science Framework. Protocols and standard operating procedures will be developed to promote replication, including in modes other than online, and all models will be hosted on the Open Science Framework [38].

## Discussion

### Overview

This study will be the first to assess question order bias in the COS for ABIs, and will help guide future trials in how to ask the COS. It is clear that the research field as a whole would benefit from reducing heterogeneity in the outcomes used in trials; thus, the findings from this study may help increase confidence in using the COS.

### Limitations and Generalizability

Respondents will be able to go back and change their responses to previous questions as they progress through the items; if the aim of the study was to capture causal connections among constructs represented by the clusters, a method used in other studies [39], then this process of changing responses would have been inappropriate. However, the aim of the study is to capture question order bias among the items as they would be used in a regular survey or trial; thus, not allowing participants to change previous responses would reduce generalizability. However, if this trial finds evidence of question order bias, then future trials should test not allowing previous responses to be changed with the aim of testing causal connections.

There is no reason to collect and verify any unique identifiers or means of contact for each participant (eg, phone number of email), since this trial does not require any follow-up. This, however, also means that there is no way of connecting group allocation to such a unique identifier. Instead, we will use HTML5 storage and cookies in participants’ web browsers to store group allocation information, such that when participants return to the study website, they will not be rerandomized. However, participants could be rerandomized if they join using a different computer or web browser. This is a limitation of this trial that we find necessary in order to retain interested individuals in the trial, as confirming email addresses and phone numbers would increase participant burden and reduce the participation rate. We will, however, keep track of the number of times each participant visits our website using the same device. A high rate of return from the same device would increase the likelihood that participants also visit from other devices, and vice versa. Therefore, we can use this measure to help judge the risk of bias from double randomization. In addition, the links to websites with alcohol information at the end of the survey aim to satisfy the need of participants to search for this material again, reducing the risk that they revisit the study website.

As is often the case in online studies, participants sign up to the trial on their own. We have no screening questions to exclude participants who are not seeking help with their alcohol consumption, as this may interfere with the study of the order effects. Therefore, some may participate because they are curious about the study or seeking help for others. A single question at the end of the survey (not part of the factorial allocation) will explore participants’ intentions (“Was the aim of your participation in this study to get help to reduce your alcohol use?”). We will also analyze the search strings used by those clicking on the advert to capture the intentions of the study sample. We will not, however, make any adjustments to our primary analyses, but rather consider this uncertainty a limitation of generalizability of the findings of the trial.

Other limitations of this trial include clustering of certain outcomes in the COS. Alternative clustering may reveal different findings, and it would also be possible to randomize the order of each question without clusters; however, the number of arms would exceed what is feasible for factorial trials. The findings may also not apply to modes other than online data collection (eg, order effects may not hold in paper-based or face-to-face administration).

